In the villages/clusters randomized to home zinc, parents will be supplied with one 10-day blister pack of zinc and 3 satchets of ORS for each child in the house under 5 years of age. Zinc packs and ORS satchets will be given once every 2 months, regardless of whether the zinc was used in the previous month. Parents will be given instructions on how to use zinc and ORS at the beginning of the study and every 2 months thereafter when the zinc is given to them by a village reporter (a traditional birth attendant) or a community health worker. Parents in these villages/clusters will also be instructed to take their children to the clinic if they have diarrhea. They will be specifically instructed that taking zinc and ORS should not prevent them from taking their child to the clinic. Particular emphasis will be made that any child with diarrhea, *and* another symptom such as fever or cough, should definitely be taken to the clinic – that zinc is not adequate treatment for a child with fever or cough, who might need an antimalarial or an antibiotic. If the field worker on his biweekly visit finds out that the mother has given zinc to a child not meeting the diarrhea case definition, he will not tell the mother to stop the course of zinc. This is for several reasons. First, the field worker will not be medically trained and so will not be trained to apply the case definition of diarrhea. Second, diarrhea is a symptom taken by history, so that if the mother reports the child has diarrhea, the field worker will not really be able to assess the accuracy of that symptom. Third, there will be no adverse effects from the course of zinc – daily zinc supplementation regardless of illness has been shown to be beneficial in some studies (Zinc Investigators Collaborative Group 1999, Zinc Investigators Collaborative Group 2000). However, the field worker will encourage all mothers of children with diarrhea, especially those with fever, cough or another symptom, to go to the clinic to be seen by a clinical officer. The use of zinc for episodes of diarrhea will be evaluated on a biweekly basis based on the data collected by the field workers to assure that zinc is not being given alone when the child has other symptoms, such as fever and cough. If a significant number of mothers are giving zinc inappropriately without seeking care for other symptoms, further education in the use of zinc in the home will be given. Community health workers or village reporters, different from the field workers who do the biweekly visits, will make home visits every month during the first 3 months of the study to ensure that mothers understand the proper use of zinc and ORS for treatment of diarrhea. After the first three months, the village reporter or community health worker will visit the home every 3 months. On each home visit, the village reporter will ask some questions to assess whether mother is using zinc correctly (appendix L).

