
At the clinic, the child will be evaluated by a clinical officer. If the child meets the above definition of diarrhea, the clinical officer will inquire if they are already taking zinc for this episode of diarrhea. If they are not already taking zinc and ORS, he will give them zinc and ORS as described below.

Along with instructions regarding how to take zinc, parents will be instructed in the use of ORS and proper fluid management (i.e. encouragement of breastmilk, if breast-feeding, ORS, or food-based fluids, such as soup, enriched uji). Recommended ORS amounts will follow KMOH guidelines. In the first 4 hours, the amount of ORS recommended will be as follows:

| Age | Up to 4 mos | 4-11 mos | 12 mo – 2 yr | 2-5 yrs |
| --- | --- | --- | --- | --- |
| Weight | < 6 kg | 6-<10 kg | 10-<12 kg | 12-19 kg |
| In ml | 200-400 | 400-700 | 700-900 | 900-1400 |

This should be followed by replacement for each loose stool as follows: up to 2 years of age 50-100 ml per stool and 2 years or more 100-200 ml.

Zinc will be administered using the same formulation in the home and in the clinic. Zinc will be administered in the form of a dispersible tablet of zinc-sulfate, 20 mg. A half-tablet, 10 mg, will be administered to children between 2 and 5 months of age. A full 20 mg tablet will be given to children > 6 months of age. The tablet will be dissolved in water, ORS or breast milk and administered to the child. . Mothers will be instructed on using clean water to dissolve tablets for remaining doses. Children who vomit after taking their dose of zinc will not be given another dose that day. The mother will be instructed how to administer the zinc tablet. Zinc will be given once daily for 10 days total. Zinc will be provided in a dispersible zinc tablet and packaged in a 10 tablet blister pack. If the child is holding down fluids and has not vomited in the past 2 hours, then zinc treatment should be started, otherwise the caretaker will be instructed to wait until this occurs.

*Referrals.* If on the day of the field interviewer’s visit, the child has any of the following conditions on the day that the field worker visits the home, the child will be referred to the health clinic

- Diarrhea with
  - moderate to severe dehydration (defined according to IMCI as having 2 or more of the following symptoms: lethargic/unconscious, sunken eyes, not able to drink or breastfeed, skin pinch goes back slowly, restless/irritable) or not able to take ORS

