  - Continued illness by the 7th day observation
  - bloody diarrhea
  - persistent diarrhea at any point in the study will be referred to Lwak hospital . Persistent diarrhea is defined as > 14 days of diarrhea.

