### History of fever in the last 24 hours

- Cough and difficult or fast breathing

Care at Lwak clinic for children in the study will be free of charge. Children in the study will be identified at the clinic by an identification card.

*Clinic visits.* All study children will be identified in the clinic by an identification card. They will be seen by a clinical officer hired by the study. Diagnosis and treatment will be according to standard protocols used for childhood illness in peripheral health facilities in Kenya (IMCI. Zinc and low osmolarity ORS will be administered according to MOH protocol. For children in the home zinc group, the clinical officer will inquire if the child is already taking zinc for that episode of diarrhea. If so, then no more zinc will be given. If not, then a 10 day course of zinc will be given. Bloody diarrhea will be treated with nalidixic acid. Uncomplicated malaria will be treated according to KMOH guidelines, artemether/lumefantrine (coartem) as of June 2006. Pneumonia not requiring referral to hospital will be treated with cotrimoxazole or amoxacillin. Children meeting criteria for referral to the hospital according to IMCI guidelines will be hospitalized at Lwak Hospital, and transferred to Bondo District Hospital or Nyanza Provincial Hospital, if appropriate treatment cannot be given at Lwak..

Children with a recent history of or documented fever will have a blood smear for malaria taken. If the results of the blood smear are positive for malaria, the child will be treated for malaria as outlined above. Blood smears will be read by a microscopist at the clinic.

A questionnaire will be filled out for study children who visit the clinic. The questionnaire will ask about symptoms, duration of illness and health-seeking behaviour (Appendix E).

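### The home-visit referral list has no stand-alone trigger for a general danger sign, so a child with such a sign but no current diarrhea, recent fever or respiratory trigger meets no stated criterion

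*Protocol*

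**What the plan says.** Under Study design, the Referrals paragraph says that a child with "any of the following conditions on the day that the field worker visits the home, the child will be referred to the health clinic". The conditions are:

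- **Diarrhea**, with any of: "moderate to severe dehydration (defined according to IMCI as having 2 or more of the following symptoms: lethargic/unconscious, sunken eyes" and three further signs), or inability to take ORS; "Continued illness by the 7th day observation"; blood in the stool; or persistence beyond 14 days.
- **Fever**: "History of fever in the last 24 hours".
- **Respiratory**: "Cough and difficult or fast breathing".

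The paragraph on follow-up of diarrhea cases applies the same criteria at the 7-day visit. The paragraph on administration of zinc states that "the field worker will not be medically trained". It adds that "the field worker will encourage all mothers of children with diarrhea, especially those with fever, cough or another symptom" to attend the clinic.

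Appendix C, the household morbidity form, has rows for vomiting everything, inability to drink or breastfeed, convulsions, and lethargy or unresponsiveness. Appendix E, the clinic sick-visit form, groups the same four as danger signs and notes that a child with any one of them will probably need referral. Its only referral question, in Part 3, is about hospital care.

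**The concern.** The field worker is the study's regular contact with the child between clinic visits, and the list is the only stated rule for when that contact must lead to care. A worker without clinical training will rely on it more than a clinician would.

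The protocol already recognizes the four danger signs and already has them recorded at home. The home rule nevertheless uses only two of them, and only when diarrhea is present. At stake is the safety of a child who is seriously ill without fever, diarrhea or breathing trouble on the day of the visit. No estimate, test or sample-size figure depends on this.

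**Working it through.** There is no figure in the plan to reproduce, so the check sets the four danger signs of Appendix E, Part 2 against the home list and the household form.

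| Danger sign | Home list, child with current diarrhea | Home list, child without diarrhea | Appendix C |
|---|---|---|---|
| Unable to drink or breastfeed | One of the five dehydration signs, two needed; inability to take ORS also counts | No trigger | Calendar row |
| Vomits everything | Not named; inability to take ORS may apply | No trigger | Calendar row |
| Convulsions | Not named | No trigger | Calendar row |
| Lethargic or unconscious | One of the five dehydration signs, two needed | No trigger | Calendar row and day-of-visit row |

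The third column assumes no fever in the previous 24 hours and no cough with difficult or fast breathing, since either would trigger referral by itself.

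Next, could any other part of the protocol supply the missing trigger?

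1. **Children with diarrhea.** Parents in both arms are told to bring a child with diarrhea to the clinic, and field workers encourage this. These children are largely covered whatever the list says, so the gap concerns children without current diarrhea.
2. **The 7-day visit.** It reuses the same list. The additional instruction to return to the clinic applies when significant diarrhea continues. Appendix D has a row for referral but no criteria of its own.
3. **Advice to parents.** The Benefits paragraph names severe diarrhea, fever, and cough or difficulty breathing. No danger sign is named.
4. **Adverse events and incidents.** Severe vomiting is a solicited event, defined by more than 72 hours without being able to breastfeed or drink, and protracted vomiting is classed as unexpected. Field workers can bring such events to the principal investigator. This route leads to reports to the investigator and the ethics bodies; it does not tell the worker to send the child to the clinic.
5. **Severe pneumonia definition.** The same four signs appear there, but they require cough or difficulty breathing and apply to children already at the clinic.
6. **Appendix C.** Its instructions call for a dehydration assessment only when diarrhea is current, and it has no row for referral.

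None of these supplies a stand-alone trigger.

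**The case against.** The strongest reply is that the list sets mandatory triggers and does not forbid other referrals. Care at Lwak clinic is free for study children, and it is hard to imagine a worker leaving a convulsing child at home. That is fair as a prediction of behavior. It does not make the written rule adequate for staff described as not medically trained.

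Three further points stand in part:

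- **Day 7.** The item "Continued illness by the 7th day observation" says illness, not diarrhea, so it could be read to cover a child who is still unwell after diarrhea has stopped. It sits under the diarrhea item, however, and applies at one visit only. It is ambiguous and does not close the gap.
- **Appendix E.** A reader might infer that the home list contradicts the clinic form. It does not: the form's only referral question concerns transfer from clinic to hospital, and its note says only that referral is likely. The form supports a narrower inference: a sign that probably warrants hospital care warrants at least a clinic review.
- **Appendix C.** Three of the four signs appear there only as calendar rows, so an entry may describe a past day. A trigger should therefore refer to the current illness.

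A reader might also infer a hazard tied to zinc. The protocol states that "Zinc will be given once daily for 10 days total" and assumes episodes of 3 ± 1 days. If zinc starts on the first day and the course is completed, 10 − 4 = 6 to 10 − 2 = 8 zinc days follow the end of diarrhea. This does not measure exposure to the gap, because the list acts only on visit days: every two weeks, plus one visit 7 days after a new episode is identified. The gap is the same in both arms, with or without zinc. The documents do not link zinc to convulsions, lethargy or inability to drink. For vomiting after zinc, the Risks paragraph reports that 91% of affected children vomited once only.

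**Conclusion.** The gap is real and narrow. Read literally, the home list gives no instruction to refer a child in either arm who has a general danger sign but no current diarrhea, no fever in the last 24 hours and no cough with difficult or fast breathing. Incident reporting and a broad reading of the day-7 item soften this without closing it.

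Its size cannot be given. The documents contain no frequency of danger signs at home visits. That none of the four signs triggers referral in such a child follows from how the child is defined and is not a measure of impact. Many seriously ill children will also have fever or diarrhea and will be referred under the existing list. The conclusion rests on a literal reading of the list as a worker's rule and on the list being complete as printed. It has no bearing on the primary analysis, sample size or error rates. It is a cheap improvement to participant safety.

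**What to change.** Add a separate item to the Referrals paragraph, applied at all home visits: any general danger sign (unable to drink or breastfeed, vomits everything, convulsions in the current illness, lethargic or unconscious), with or without diarrhea: refer to the clinic the same day. Keep the two-sign rule for the dehydration item only. Optionally, add to Appendix C the referral row that Appendix D already has, so that the action is recorded beside the sign.

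The cost is one protocol line and, if wanted, one form row. The planned two-week field-worker training already includes referral criteria. The downside is some additional referrals to free clinic care.

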### History of fever in the last 24 hours

- Cough and difficult or fast breathing

Care at Lwak clinic for children in the study will be free of charge. Children in the study will be identified at the clinic by an identification card.

*Clinic visits.* All study children will be identified in the clinic by an identification card. They will be seen by a clinical officer hired by the study. Diagnosis and treatment will be according to standard protocols used for childhood illness in peripheral health facilities in Kenya (IMCI. Zinc and low osmolarity ORS will be administered according to MOH protocol. For children in the home zinc group, the clinical officer will inquire if the child is already taking zinc for that episode of diarrhea. If so, then no more zinc will be given. If not, then a 10 day course of zinc will be given. Bloody diarrhea will be treated with nalidixic acid. Uncomplicated malaria will be treated according to KMOH guidelines, artemether/lumefantrine (coartem) as of June 2006. Pneumonia not requiring referral to hospital will be treated with cotrimoxazole or amoxacillin. Children meeting criteria for referral to the hospital according to IMCI guidelines will be hospitalized at Lwak Hospital, and transferred to Bondo District Hospital or Nyanza Provincial Hospital, if appropriate treatment cannot be given at Lwak..

Children with a recent history of or documented fever will have a blood smear for malaria taken. If the results of the blood smear are positive for malaria, the child will be treated for malaria as outlined above. Blood smears will be read by a microscopist at the clinic.

A questionnaire will be filled out for study children who visit the clinic. The questionnaire will ask about symptoms, duration of illness and health-seeking behaviour (Appendix E).

*Follow-up of cases of diarrhea.* Children identified as having a new episode of diarrhea on the routine biweekly household visit or in the clinic will be visited 7 days later. Referrals will be made on these visits according the criteria listed above under G. A short questionnaire regarding ongoing symptoms and signs of illness, interim health care seeking, and possible side effects to the study medication will be administered (Appendix D). No additional zinc or ORS will be given by the field worker on follow-up visits. If the child is still having significant diarrhea at the follow-up visits, the field worker will instruct the mother to take the child back to the clinic (or to the clinic if they have not gone yet.) The child will next be visited on day 14 according to the regular weekly visit schedule.

*Definition of study outcomes.*

- 1. Diarrhea – A diarrheal day will be considered a day in which the child has 3 or more loose or watery stools. New episodes of diarrhea will be defined as at least one diarrheal day without diarrhea in the previous 72 hours. A severe diarrheal episode will be defined as an episode in which children go to the clinic to receive care for the episode.
  2. Acute Respiratory Infections.
     1. Clinical ALRI - An episode of acute lower respiratory illness (ALRI) will be defined for the home visits as a history of cough or difficulty breathing for > 2 days. An ALRI day will be considered a day that is part of an ALRI episode in which a child has cough or difficulty breathing. New episodes of ALRI will be defined as an ALRI episode without an ALRI day in the previous 72 hours. Acute respiratory infection (ARI) will include any child with cough (of any duration), difficulty breathing, or ear pain and/or discharge.
     2. Pneumonia – Pneumonia and severe pneumonia will be defined for children who visit the clinic and meet the IMCI criteria:
        1. Pneumonia in children < 5 years of age -- Cough or difficulty breathing *and* Respiratory rate > 50/minute for 2-11 month old, >40/minute for 1-4 years
        2. Severe pneumonia in children 1 month - 5 years of age

Cough or difficulty breathing and

- - - - 1. chest indrawing
        2. stridor in a calm child
        3. a general danger sign

Unable to breastfeed or drink

Vomits everything

Convulsions

Lethargy or unconscious

- 1. Malaria -
     1. Clinical malaria – History of fever in the preceding 24-48 hours as reported by the caretaker
     2. Parasitologic malaria – History of recent fever or documented fever and a blood smear positive for asexual malaria parasites.

*Adjuvant therapies*. Children who have not received Vitamin A in the prior 6 months in both groups will be given Vitamin A at the start, 6 months, and end of the study, according to KMOH guidelines, dosed according to age. Children in both groups 2 years of age or older who have not received mebendazole or albendazole in the prior 6 months will receive mebendazole 500 mg at the start, 6 months, and end of study, according to KMOH guidelines.

*Compliance monitoring*. Compliance will be monitored by asking the child’s caretaker how many pills she gave the child. In addition, caretakers will be asked to keep the blister pack and the number of pills remaining on the day 7 and 14 day visit will be counted and recorded.

## Adverse Events and Incidents

The recording and reporting of adverse events and incidents fall into two categories – solicited adverse events and reporting of incidents to Human Research Committees. These two categories will be described separately.

## Solicited Adverse Events.

Solicited Adverse Events are potential side effects to the treatment of diarrhea, zinc and/or ORS that occur up to 24 hours after the last dose, and will be ascertained from the 3 and 7-day visits by the field worker using a standardized questionnaire (Appendix E). These may or may not be reportable incidents, depending on whether they meet the definitions below.

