### Definitions for solicited adverse events

Solicited adverse events include the systemic reactions of fever, irritability, nausea, vomiting, and rash. (Appendix D)

Definitions of Solicited AEs:

Fever: as reported by the mother/caretaker or the field worker taking axillary temperature of 38ºC (100.4ºF), recorded by digital thermometer. Severe defined as > 72 hours of fever after administration of zinc and/or ORS.

Irritability. Activity or behaviour deemed to be unusual in intensity or duration compared with child’s normal behaviour as reported by the mother/caretaker. Severe defined as > 72 hours of irritability after administration of zinc and/or ORS.

Nausea. Complaint of being nauseated in verbal children as reported by the mother/caretaker after administration of zinc and/or ORS.

Vomiting. An episode of vomiting will be defined as at least one episode of vomiting occurring within 60 minutes of zinc administration in a child previously stable and not having vomited for at least 60 minutes prior to receiving zinc. Severe defined as not being able to breastfeed or drink anything for > 72 hours after administration of zinc and/or ORS, as reported by the mother.

Rash. Unusual redness, texture or swelling of skin that was not present before administration of study drug. Severe defined as involving mucosal membranes at any time, or having a duration of > 72 hours after administration of zinc and/or ORS.

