# Time frame

*Training.* A two-week training will be conducted to train field workers in administration of consent, questionnaire administration, use of ORS and zinc administration and referral criteria.

*Consent phase.* All eligible households in the 33 selected villages will be offered participation in the surveillance. In each household with a child under 5 years of age, a caretaker of the child must sign an informed consent form allowing participation of the child. The consent phase will take approximately 2 weeks. Community consent will be obtained by having an initial meeting with the chiefs and subchiefs of the area, followed by biannual update meetings. In addition, barazas (talks) will be held with community groups, such as churches and women’s groups, to sensitize them to the project.

*Length of study.* The active phase of the study in whichweekly household visits will be made will last 1 year.

*Expected time to publication.* The study will be analyzed and prepared to submit for publication 6 months after the end of the study.

Ethical considerations

*Risks.* Zinc has been administered to over 35,000 children in the ICDDR.B Cholera Hospital in Dhaka without excess mortality.

Zinc can lead to an increase in vomiting. In one study in Nepali children there was a two-fold increase in vomiting (Strand, 2002). Another recent study in Bangladesh showed that more children vomited in the course of their treatment when taking dispersible zinc tablet than among children who did not get zinc -- overall 20% vomited; 40% due to zinc, 26 % placebo, and 34% due to the illness. (Larson 2005). There was also an increase in regurgitation in children who got zinc versus those who did not (8.6% zinc 4.1% placebo, 1.5% nothing. However, it should be noted that most children who vomited after zinc administration had a history of vomiting within the last 24 hours. Moreover, 91% of children who vomited after zinc administration only vomited once.

A small bruise or mild pain on the finger from where the fingerstick blood sample is taken may develop.

The only other risk of being in the study will be minor inconveniences to the family resulting from the brief amount of time necessary to complete the questionnaires every other week, or on days 3 and 7 after diarrheal episodes.

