**Appendix E. Clinic Sick Visit questionnaire**

**Part 1: Identifying information**

Date  / / 

Child’s First/Christian Name Juok/middle Name Last/Father’s name

DSS Permanent ID Number.  Child’s age in months 

What is relationship of the caregiver to the child? ?  Self  Mother  sister  father  grandmother  aunt  adopted mother/guardian  Other ­­­­­­­­­­­­­­­­­­­­­­­­­­­­­­­

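### Three of the five solicited adverse events (nausea, vomiting and severe rash) cannot be fully derived from the follow-up form meant to collect them

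*Protocol*

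**What the plan says.** The Protocol's section on solicited adverse events says that side effects are ascertained at home visits "by the field worker using a standardized questionnaire (Appendix E"). The form with that letter is headed "Appendix E. Clinic Sick Visit questionnaire", and the paragraph on clinic visits uses it that way: "The questionnaire will ask about symptoms, duration of illness and health-seeking behaviour (Appendix E").

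Two other places name a different form. The definitions section has: "Solicited adverse events include the systemic reactions of fever, irritability, nausea, vomiting, and rash. (Appendix D"). The paragraph on follow-up of diarrhea cases says that a short questionnaire covering "possible side effects to the study medication will be administered (Appendix D"). Appendix D is the diarrhea follow-up form, one per episode, with a code of 1, 0 or 9 for each symptom on each calendar day.

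Three of the definitions matter here:
- **Nausea**: "Complaint of being nauseated in verbal children as reported by the mother/caretaker", after zinc and/or ORS.
- **Vomiting**: at least one episode within 60 minutes of zinc, in a child previously stable and "not having vomited for at least 60 minutes prior to receiving zinc".
- **Severe rash**: mucosal membranes involved at any time, or a duration above 72 hours.

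**The concern.** The definitions and the forms are both printed in the Protocol, and they do not match. A solicited event should be asked about at every scheduled contact. If the form has no item for it, or no item for a condition that its definition imposes, the event cannot later be counted as the Protocol says it will be. These are caretaker reports over a short recall period, so what is not asked cannot be recovered at analysis.

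Vomiting matters most. The Risks paragraph under Ethical considerations treats it as the main known harm of zinc, and the section on reporting of incidents names vomiting after the first dose as the expected event. The Risks paragraph also notes that "most children who vomited after zinc administration had a history of vomiting within the last 24 hours". The vomit-free interval before the dose is what separates vomiting linked to the dose from vomiting that belongs to the illness, and that interval is the part not recorded. The Ministry of Health is to use the trial in deciding on community roll-out, so the tolerability record has a use beyond the trial.

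**Working it through.** The Protocol states no figure on this point, so the check sets each definition beside the items on Appendix D.

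| Event | What the definition needs | What Appendix D records | Derivable as defined? |
| --- | --- | --- | --- |
| Fever | Caretaker report or measured temperature; severe if above 72 hours | Daily fever row; temperature on the day of the visit | Yes (72 hours only to whole days) |
| Irritability | Caretaker report; severe if above 72 hours | Daily irritable/restless row | Yes (72 hours only to whole days) |
| Nausea | Complaint by a verbal child | Nothing | No |
| Vomiting | Vomiting within 60 minutes after zinc **and** none in the 60 minutes before; severe if unable to breastfeed or drink for above 72 hours | Vomiting in the hour after zinc; daily vomiting/spit-up row; daily not-eat/drink row | In part: post-dose yes, severe grade roughly, pre-dose condition no |
| Rash | New rash; severe if mucosal at any time or above 72 hours | One daily rash row | In part: presence and duration yes, mucosal criterion no |

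Result: 2 of 5 events are obtainable, 1 of 5 is wholly absent, and 2 of 5 lack one defining criterion.

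**Can the missing criteria be inferred from other rows?**
- *Vomiting.* No. The rows are coded by calendar day without clock time. A child who vomits after the dose can have a 1 in the daily vomiting row whether or not vomiting also came before the dose. The daily row therefore cannot separate the two cases on the days that matter.
- *Rash.* Only when the rash lasts above 72 hours, since it is then severe on duration anyway. A mucosal rash of 72 hours or less is severe by definition but would be graded non-severe from Appendix D.

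**Do other forms supply the items?**
- Nausea is on none of the forms supplied (Appendices B to H and J to L).
- Appendix E asks about any vomiting, with no timing relative to a dose, and its treatment list does not include zinc. Following the Appendix E citation literally would lose information that Appendix D has.
- For mucosal reactions, Appendix E has a mouth-ulcer item and names mucocutaneous reaction as an example under one question on unanticipated events. Appendix F has a tick box. The first needs a clinic visit and the second an opened incident.

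**Direction of error.** Vomiting would tend to be over-counted against its own definition. Nausea would be missing, and severe rash under-recorded at home visits.

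**The case against.** The strongest reply concerns vomiting. The section on administration of zinc says that treatment starts only when the child is keeping fluids down and has not vomited in the past 2 hours. That interval is longer than 60 minutes, so at the start of treatment it largely enforces the pre-dose condition. The Protocol also singles out the first dose as the one expected to provoke vomiting, and it cites a finding that 91% of children who vomited after zinc vomited only once. This stands in part. It narrows the gap for the first dose. But the 2-hour condition is an instruction and not a recorded item, so adherence cannot be checked, and it is not clearly applied to the later daily doses.

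Other points on that side also stand:
- Mucosal reactions have a route through the clinic and incident forms, and interviewers may bring events to the principal investigator's attention. That route is not systematic.
- Nausea applies only to verbal children and has no severe grade.
- Forms are to be field tested, so their wording may still change.
- No stated objective or planned comparison uses the solicited events.

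A reader might infer more than the Protocol supports, in four ways:
- *That none of the solicited events can be obtained.* Fever and irritability can.
- *That safety data will be taken on the wrong form.* The Appendix E citation occurs once and two other places give Appendix D, so it reads as a lettering slip.
- *That nausea will be reported as zero.* An item never asked is missing, not zero.
- *That most recorded vomiting would not be due to zinc.* The Risks paragraph splits vomiting in a cited study into 40% zinc, 26% placebo and 34% illness, and one might add 26% + 34% = 60%. That split comes from a placebo-controlled study and covers vomiting over the whole course of treatment. This trial has no placebo, and the form item concerns the hour after the dose. The figure cannot be carried over.

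**Conclusion.** The point holds in a limited form. Three of the five solicited adverse events are not fully derivable from Appendix D as printed: nausea not at all, vomiting without its pre-dose condition, and severe rash without its mucosal criterion.

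No numerical size can be put on the resulting misclassification. The Protocol gives neither the frequency of vomiting in the hour before a dose nor that of short mucosal rashes. The conclusion assumes that Appendix D is the intended instrument and that the forms supplied are the ones to be used; Appendices A and I are not among them. The consequence is confined to safety and tolerability data. Diarrhea prevalence, the primary outcome, is unaffected.

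**What to change.** 1. Add three rows to Appendix D, coded by day like the others: *nausea (verbal child)*, *vomited in the hour before zinc*, and *rash: mucosal involvement*.
2. State in the definitions section that a vomiting event counts only when the pre-dose item is No.
3. Change the citation in the solicited adverse events section from Appendix E to Appendix D, in line with the definitions section and the paragraph on follow-up of diarrhea cases.

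The cost is three form rows, one sentence, one corrected letter and a slightly longer follow-up interview. No extra visits or measurements are needed.
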